## Abstract

**Background/Aims:**

Strategies for an effective intervention after chronic kidney disease (CKD) screening have not been well examined. We describe the rationale and design of a protocol of a pragmatic randomized controlled trial (RCT) to test the effect of a behavioral intervention using the nudge approach in behavioral economics on CKD patients’ visiting behaviors to physicians and change in their kidney function after CKD screening.

**Methods:**

The RCT will include CKD patients (N = 4500) detected at screening (estimated glomerular filtration rate [eGFR] <60 mL/min/1.74 m^2^ or urine protein ≥1+), aged 40–63 years. The two intervention groups will receive a “usual letter” and “nudge-based letter,” while the control group will only receive a conventional follow-up. Our primary outcome is proportion of patients’ visiting physicians for 6 months after the intervention; the secondary outcome is change in the eGFR at 2 years after the intervention.

**Results:**

We developed an efficient intervention program after CKD screening and designed the pragmatic RCT to assess its effectiveness in the real world. Our trial is unique in that it investigates the effect of the nudge approach in behavioral economics. By the end of 2018, we have enrolled 1,692 participants, and randomized 677 participants into the usual letter group, 677 participants into the nudge-based letter group, and 338 participants into the control group. We have confirmed that health checkup data could identify a large number of eligible participants.

**Conclusion:**

The trial's results will contribute to filling in the gap between screening and subsequent medical interventions for preventing CKD progression.

## Introduction

1

Chronic kidney disease (CKD) is recognized as a major public health burden because it is associated with cardiovascular disease and mortality, as well as progression to end-stage renal disease (ESRD) [[1], [2], [3]]. From the perspective of health care resource utilization, a severer CKD stage is associated with higher health care cost, which is a big burden for society and the health care system [4,5]. Therefore, prevention of CKD progression is required worldwide. The first step for prevention is to identify potential CKD patients from the general population. Previous studies reported a substantial prevalence of CKD in the general population [2]; for example, 13% in Japan [6] and 11% in the United States [7].

There is a large gap between the number of potential CKD patients estimated from the laboratory results at screening and the number of diagnosed CKD patients extracted from medical records. This gap means that many of the potential CKD patients do not visit physicians to receive care for CKD. In Japan, where large-scale CKD screening is performed within the health care system [8], it is possible to clarify the actual CKD prevalence during screening of the general population and to track CKD patients' visiting behavior to physicians after CKD screening. If CKD is suspected at the health checkup based on renal function test results (urine test result and estimated glomerular filtration [eGFR]), it is recommended that patients visit a physician to confirm the presence of CKD. To maximize the effect of screening on the prevention of CKD progression, an effective intervention needs to be designed for patients suspected of having CKD in order to encourage them to appropriately visit their physicians after screening. In conventional follow-up after CKD screening in Japan, participants will be notified of their results, but there is no special intervention for offering CKD care. The intervention at that time is preferable to not be mandatory; instead, a “nudge” that respects the patient's free will is required [9]. The idea of behavioral economics and nudge approaches to healthcare is popular in public health [10].

In order to implement research to improve patients' visiting behavior to physicians after CKD screening in the general population, we launched the pragmatic trial of nudging CKD patients after screening. The trial was designed in the Japanese health care system, which has features of a universal health care system and large-scale CKD screening. The aim of the trial is to evaluate whether a behavioral intervention (i.e., a usual letter and nudge-based letter) would improve CKD patients’ visiting behaviors to physicians and protect their kidney function.

## Methods

2

### Overall study design

2.1

The pragmatic randomized controlled trial (RCT) of nudging CKD patients after screening was designed in the health care system setting [11] to examine the effect of a novel behavioral intervention among CKD patients (Fig. 1). We will identify CKD patients at screening and randomize them into three groups: “usual letter,” “nudge-based letter,” and control group. Between the groups, we will compare outcomes of patients’ visiting behaviors to physicians (visiting physicians for CKD care for 6 months after the intervention) and change in their kidney function (change in the eGFR after 2 years).

**Fig. 1 fig1:**
[figure not shown]
**Overall study design**. The pragmatic randomized controlled trial of nudging CKD patients after screening was designed in the health care system setting to examine the effect of a novel behavioral intervention among CKD patients. Identification phase: We will identify eligible CKD patients according to health checkup data. Intervention phase: We will randomize participants into three groups: “usual letter,” “nudge-based letter,” and control group. Follow-up phase: Between the groups, we will compare outcomes of patients' visiting behaviors to physicians and change in their kidney function according to medical claims and health checkup data. CKD, chronic kidney disease

### Participants and setting

2.2

We conducted this pragmatic RCT among persons insured by the Health Insurance Association for Architecture and Civil Engineering companies in Japan (HIA^2^CE), which is a large health insurance association that insures about 400,000 persons as employees and their family members. The health insurance association covers most of the architecture and engineering companies all over Japan, from local small construction companies to major general contractors.

The inclusion criteria are (a) age between 40 and 63 years, (b) patients receiving CKD screening, and (c) those with an eGFR <60 mL/min/1.74 m^2^ or positive proteinuria. Proteinuria was measured by a urine dipstick test as −, ±, 1+, or 2+. Results of urine protein ≥1 + were defined as positive proteinuria. The exclusion criteria are (a) patients with an eGFR <15 mL/min/1.74 m^2^, and (b) those with ESRD. Those criteria will be confirmed using health checkup data from April 2018 to March 2019. The eGFR will be estimated from annual health checkup data using the Japanese coefficient-modified CKD Epidemiology Collaboration equation, which has been validated in the Japanese population [12,13].

### Intervention and control

2.3

We defined two intervention groups that will receive a notification letter, the usual letter and nudge-based letter. We also defined a third group as the control group that will not receive a letter. Data collectors and those assessing outcomes will be blinded to the assignment of interventions.

In the usual letter, we provide information about CKD based on clinical evidence; recommend visits to physicians; and show patients' individual health checkup results of the eGFR, urine protein, and risk factors of hypertension (systolic blood pressure/diastolic blood pressure ≥140/90 mmHg or receiving antihypertensive drugs), diabetes (glycated hemoglobin A1c level ≥6.5% or receiving antidiabetic drugs), and smoking (current smoker or not). In the nudge-based letter, we encourage visits to physicians using the nudge approach in behavioral economics. The nudge is defined as “any aspect of the choice architecture that alters people's behavior in a predictable way without forbidding any options or significantly changing their economic incentives” [9]. In general, behavioral economics researchers consider people's seemingly irrational behaviors, procrastination [14] and loss avoidance [15], to construct a nudge-based intervention. In this study, to alter the participant's visiting behavior to physicians in a clinically desirable way without forbidding any other options, our nudge approach includes “commitment” (designing the space for intentions prompts, where participants write the visiting date and time, solidifying their intention of visiting physicians, and preventing the procrastination) [16] and “loss-framed message” (considering loss avoidance and giving information that emphasizes the loss of opportunity for preventing CKD progression and for work) [17]. We also add information about the concrete steps to visit a physician in order to decrease the participant's burden (cognitive costs). We also show individual health checkup results in the nudge-based letter as in the usual letter. The volumes of documents are similar between both the nudge-based letter and usual letter. Supplemental Fig. 1 and Supplemental Fig. 2 show the format of these letters. These letters will be sent by mail to individuals from the health insurance association. The research team is not involved in the individual shipping business of personal data, and the trial is open-labeled without blinding because it would be difficult to send a placebo letter to the control group.

Conventional follow-up after the screening will be implemented in all groups including the control group. In the Japanese health checkup system, all adults aged 40 years or older receive an annual health checkup with the aim of screening for metabolic syndrome. The participants receive notification of the abnormalities in the health checkup results regarding central obesity, hypertension, diabetes, and hyperlipidemia, but it does not include specific information about CKD. There is no special recommendation to visit physicians for CKD care in the conventional follow-up.

### Randomization

2.4

For this pragmatic trial in the health care system, a research coordinator from the health insurance association assigned eligible participants and generated a unique number for each. After stratifying patients by the timing of screening (quarterly), eGFR (≥60 mL/min or <60 mL/min), and urine protein (≥+ or ≤±), we conduct random allocation with the permuted block method for each stratum. We randomize participants in a 2:2:1 ratio into the usual letter group, nudge-based letter group, and control group, respectively.

### Outcomes

2.5

Our primary outcome is proportion of patients’ visiting physicians for 6 months after the intervention, and the secondary outcome is the change in the eGFR at 2 years after the intervention (Table 1). The primary outcomes of visiting physicians after the intervention is defined independently of the presence or absence of the visit before the intervention. Although our definition of visiting physicians after the intervention may include the follow-up visit (re-visit after the intervention with a history of visiting physicians before the intervention), this does not affect internal validity of the trial. Follow-up of participants will end at 2 years after their intervention data are collected or until they leave the HIA^2^CE.

**Table 1 tbl1:** Outcomes.

Primary outcome
**Proportion of visiting** The proportion of participants who visit physicians for CKD care for 6 months after the intervention
**Secondary outcome**
**Change in the eGFR** Change in the eGFR (mL/min/1.73 m^2^) from the pre-intervention value to the post-intervention value after 2 years
**Proportion of continuous visiting** The proportion of participants who visit physicians for CKD care at least twice between 1 year and 2 years after the intervention

CKD, chronic kidney disease; eGFR, estimated glomerular filtration rate.

The medical claims data from the intervention date to 6 months after the intervention is used to define visiting behavior. If the participants have CKD-related diagnostic codes (Table 2) in their medical claims during this period, it is considered that they visited physicians for CKD care. The health checkup data of pre-intervention and post-intervention (2 years later) is used to define change in the eGFR.

**Table 2 tbl2:** Chronic kidney disease-related diagnostic codes.

	ICD-10 codes
Chronic kidney disease	N170, N171, N172, N178, N179, N180, N188, N189, N19, N990
Tubulointerstitial nephritis	N110, N111, N118, N119, N12, N140, N141, N142, N143, N144, N150
Chronic glomerular nephritis	N002, N003, N004, N006, N007, N009, N012, N014, N016, N017, N019, N028, N029, N030, N032, N033, N034, N036, N037, N039, N040, N042, N044, N046, N049, N050, N051, N052, N053, N054, N055, N056, N057, N058, N059, N069, N079, N085
Diabetic nephropathy	E102, E112, E132, E142
Hypertensive nephrosclerosis	I129, I120
Polycystic kidney disease	Q613

### Statistical analysis

2.6

#### Sample size

2.6.1

Based on past medical claims data and results from the previous intervention, we assume that the proportions of patients visiting physicians in each group are 0.15, 0.20, and 0.25 in the control group, usual letter group, and nudge-based letter group, respectively. We set the allocation ratio as 1:2:2 for the control group, usual letter group, and nudge-based letter group, respectively. The sample sizes of 850, 1700, and 1700 patients for each group were determined to achieve ≥80% power overall and for all pairwise comparisons with the chi-square test by the simulation-based approach. The sample size provides ≥99% power to detect the difference of change from the baseline eGFR of −3 (standard deviation = 10) with a two-sided significance level of 0.05.

#### Data analysis

2.6.2

We will describe participant characteristics with means and proportions by groups and compare them between groups using analysis of variance and chi-square tests, and their non-parametric analogs, as appropriate.

In our analysis to evaluate the effect of the intervention, we will conduct an intention-to-treat analysis. In our primary analysis, we will apply a logistic regression model with a dichotomous variable of visiting behavior as the dependent variable, and dummy variables of three groups and allocation adjustment factors (quarterly timing of the intervention, eGFR, and urine protein) as the independent variables. In the logistic regression model, we will estimate p-values by omnibus tests (Wald test) for the differences in outcome (proportion of visits to physicians) between the groups. If the two-sided p-values by omnibus tests is <5%, we will conclude that there are statistically significant differences in outcome between the groups and will continue to perform pairwise comparisons in order to adjust for multiple comparisons [18]. From the logistic regression model, we will estimate risk differences and their 95% confidence intervals using the model-based standardization technique [19]. In a sensitivity analysis, we will adjust for the presence of lifestyle guidance involved in the usual follow-up after the health checkup. We will also estimate the proportion and its Wald-type 95% confidence interval of the primary outcome for each group. Further, we will estimate the odds ratio and its 95% confidence intervals, and compare them between the groups.

For the confirmatory analysis of the secondary outcome, we will apply the closed testing procedure. Specifically, only if the two-sided p-values by the omnibus test of the primary outcome are <5%, we will conduct the following analysis on the difference of the eGFR. We will apply a linear regression model with the difference of the eGFR as the dependent variable, and dummy variables of the three groups and allocation adjustment factors (quarterly timing of the intervention, eGFR, and urine protein) as the independent variables. We will estimate p-values by omnibus tests (Wald test) to determine differences in outcome (i.e., the difference of eGFR) between the groups. If the two-sided p-values by omnibus tests are <5%, we will conclude that there are statistically significant differences in outcome between the groups and will continue to conduct pairwise comparisons.

In the subgroup analysis, we will assess the effect of the interventions by the presence of diabetes, age categories (40–49, 50–59, and ≥60 years), sex, and past CKD detection.

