## Results

3

Among 37,775 participants, aged between 40 and 63 years, who received a health checkup between April and June in 2018, we have enrolled 1,692 CKD participants (4.5%). The selection process of study participants during this period is summarized in Fig. 2. Then we randomized 677 participants into the usual letter group, 677 participants into the nudge-based letter group, and 338 participants into the control group. We confirmed that a large number of eligible participants for the trial could be identified by routinely collected health checkup data. Table 3 shows participant characteristics in each group. Middle-aged men are the focus of our study participants. Age, eGFR, proportion of patients with urine protein ≥1+, blood pressure, and HbA1c level were similar between the groups. The proportion of patients with a previous visit was slightly higher in the control group than in the intervention group (no statistical test). We will continue to select eligible participants by the end of March 2019 and follow them until their health check-up at 2 years later.

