**Fig. 2 fig2:**
[figure not shown]
**Selection process of study participants, from 2018 April to 2018 June.** Among 37,775 participants, aged between 40 and 63 years, who received a health checkup between April and June in 2018, we have enrolled 1,692 CKD participants (4.5%). CKD, chronic kidney disease; eGFR, estimated glomerular filtration rate; ESRD, end stage renal disease.

**Table 3 tbl3:** Participant characteristics.

	Control group (N = 338)	Usual letter group (N = 677)	Nudge-based letter group (N = 677)
Age, mean (SD), years	53.7 (6.6)	53.8 (6.5)	53.6 (6.6)
Male sex, n (%)	313 (92.6)	617 (91.1)	623 (92.0)
eGFR, mean (SD), mL/min/1.73 m^2^	68.7 (15.2)	68.1 (16.0)	68.7 (15.9)
Urine protein ≥+, n (%)	214 (63.3)	429 (63.4)	429 (63.4)
SBP, mean (SD), mmHg	129.8 (17.9)	129.9 (18.7)	130.2 (18.7)
DBP, mean (SD), mmHg	81.9 (13.0)	82.2 (12.9)	82.0 (13.0)
HbA1c, mean (SD), %	6.1 (1.1)	6.0 (1.1)	6.10 (1.22)
Hypertension, n (%)	138 (37.2)	252 (40.8)	264 (39.0)
Diabetes, n (%)	66 (19.5)	100 (14.8)	108 (16.0)
Current smoking, n (%)	120 (35.5)	217 (32.1)	229 (33.8)
Previous visiting,^a^ n (%)	19 (5.6)	31 (4.6)	28 (4.1)

SD, standard deviation; eGFR, estimated glomerular filtration rate; SBP, systolic blood pressure.

DBP, diastolic blood pressure; HbA1c, glycated hemoglobin A1c; CKD, chronic kidney disease.

a Previous visiting was defined as proportion of visiting to physicians within 6 months before health checkup.

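### The primary logistic model omits previous CKD visiting, a baseline version of the outcome that the trial already holds, and so forgoes a free gain in precision

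*Protocol article*

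**What the plan says.** **Model.** Section 2.6.2 (Data analysis) gives the independent variables of the primary logistic model as "dummy variables of three groups and allocation adjustment factors (quarterly timing of the intervention, eGFR, and urine protein) as the independent variables". Section 2.4 (Randomization) stratifies on the same three factors. The only further adjustment named is a sensitivity analysis for lifestyle guidance. Past CKD detection is listed as a subgroup factor, but it is not a covariate and is not defined as a previous visit.

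**Outcome.** Section 2.5 (Outcomes) says that the primary outcome "is defined independently of the presence or absence of the visit before the intervention" and that it "may include the follow-up visit (re-visit after the intervention with a history of visiting physicians before the intervention". Any Table 2 diagnostic code in the claims for the 6 months after the intervention counts. The section adds that this leaves internal validity intact.

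**Data held.** Table 3 reports previous visiting as 19/338 (5.6%) in control, 31/677 (4.6%) in usual letter and 28/677 (4.1%) in nudge-based letter. Its footnote reads: "Previous visiting was defined as proportion of visiting to physicians within 6 months before health checkup". Section 3 (Results) comments: "The proportion of patients with a previous visit was slightly higher in the control group than in the intervention group", and notes that no test was done.

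**Power.** Section 2.6.1 (Sample size) assumes visiting proportions of 0.15, 0.20 and 0.25 with 850, 1700 and 1700 patients, and claims at least 80% power overall and for all pairwise comparisons.

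**The concern.** A person already under CKD care before the checkup can meet the primary outcome simply by continuing that care, whichever letter arrives or none. Previous visiting therefore marks a small group whose outcome is probably high in every arm. A covariate of that kind removes outcome variance that the letters cannot influence.

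The article fixes the covariate list explicitly and leaves this variable out. At stake is precision, chiefly for control versus usual letter, which combines a 5-point assumed difference with the small control arm and is the least powered of the three comparisons. The plan already fits a logistic model and standardises it to risk differences, so the gain would need one extra binary term and no new data.

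**Working it through.** **1. The plan's own power.** Pooled chi-square, two-sided 5%, normal approximation, 850/1700/1700 at 0.15/0.20/0.25:

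- control vs usual letter: 87.7%
- usual vs nudge letter: 93.7%
- control vs nudge letter: above 99.9%
- omnibus test: above 99.9%
- all three pairs significant together after the omnibus test (200,000 simulated trials): 81.5%

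The stated figure of at least 80% is reproduced, whether it is read for each pair or for all pairs jointly.

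**2. How prognostic could previous visiting be?** Pooled prevalence is q = (19 + 31 + 28)/1692 = 78/1692 = 4.6%. The re-visit rate r₁ is not in the documents and is assumed to lie between 50% and 90%. Holding an arm's overall rate at p, the rate among people with no previous visit is r₀ = (p − q·r₁)/(1 − q). The share of outcome variance explained is q(1 − q)(r₁ − r₀)²/[p(1 − p)].

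Example for control, p = 0.15, r₁ = 0.9: r₀ = (0.15 − 0.0415)/0.954 = 0.114. The share is 0.046 × 0.954 × 0.786²/0.1275 = 0.21.

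| Assumed r₁ | p = 0.15 | p = 0.20 | p = 0.25 |
|---|---|---|---|
| 50% | 4.6% | 2.7% | 1.6% |
| 70% | 11.4% | 7.5% | 5.2% |
| 90% | 21.3% | 14.8% | 10.9% |

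**3. Power with and without the covariate.** Simulated trials (6,000 per row), Wald omnibus test then Wald pairwise tests, stratification factors left out, q = 4.6%:

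| Assumed r₁ | Control vs usual: unadjusted → adjusted | All three pairs: unadjusted → adjusted |
|---|---|---|
| 50% | 87.8% → 88.8% | 81.4% → 82.7% |
| 80% | 88.4% → 91.9% | 82.0% → 87.6% |
| 90% | 87.7% → 93.1% | 81.6% → 89.4% |

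A separate simulation gives the standard error of the control-versus-usual risk difference. It falls from 0.01584 to 0.01549 (2%) at r₁ = 50%, from 0.01571 to 0.01490 (5%) at 70%, and from 0.01588 to 0.01424 (10%) at 90%.

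The Conclusions section gives 7–8% visiting before screening. At q = 7.5%, adjusted power for control versus usual is about 92% (r₁ = 70%) or 96% (r₁ = 90%).

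**4. The first-quarter imbalance.** The three-arm chi-square is 1.13 on 2 df, p = 0.57. Control versus nudge differs by 1.5 points (p = 0.29) and control versus usual by 1.0 point (p = 0.47). If these differences held through all enrolment, the shift in nudge minus control would be about −(0.0562 − 0.0414) × (r₁ − r₀):

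- using the control-arm gap: 0.0149 × 0.367 = 0.5 points at r₁ = 50%, and 0.0149 × 0.786 = 1.2 points at 90%
- averaging the gap over the two arms: 0.47 and 1.09 points

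If later quarters are balanced, these shrink by 338/850 = 0.40. The averaged-gap figure at 90% becomes 0.43 points and the control-gap figure 1.17 × 0.40 = 0.46, so roughly 0.4 points is the upper end. The assumed nudge effect is 10 points.

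**The case against.** The strongest reply is that nothing in the plan is wrong. Adjusting for exactly the stratification factors is standard. Randomisation protects the type I error, the confidence interval already allows for chance imbalance, and the statement in section 2.5 on internal validity is correct. The power target is met without the extra term. All of this stands, and it limits the point to efficiency. It does not remove the point, because section 2.5 answers a question of validity and says nothing about precision.

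A reader might infer from Table 3 that a known imbalance will bias the result. The documents do not support that. The figures rest on 78 people among 1,692 of the 4,250 planned, enrolment was continuing to March 2019, and the differences are compatible with chance. Control has more previous visitors, so any carry-over would understate the letters' effect against control. Choosing a covariate because of an observed imbalance would also be poor practice.

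A reader might also take it as established that previous visiting predicts the outcome strongly. That is an inference from the outcome definition. No re-visit rate is reported, and at the lower end of the assumed range the gain is only about one power point.

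Finally, adding the covariate changes the meaning of the planned odds ratio. This is true and should be stated in the plan. The standardised risk difference keeps its meaning.

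**Conclusion.** The point holds as a missed improvement, not as an error or a bias. The primary model omits a baseline version of the outcome that the trial already holds. Including it would add about 1 to 6 power points for control versus usual letter, and about 1 to 8 points for all three pairs together, where unadjusted power is only a little above the 80% target.

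These sizes rest on an assumed re-visit rate of 50–90% that is the same in every arm, on 4.6% previous visitors, and on simulations without the stratification factors. The gain would be larger at the 7–8% given in the Conclusions, which does not agree with Table 3. The imbalance seen so far adds nothing to the case.

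**What to change.** 1. Before any outcome data are seen, add previous visiting to the primary logistic model and to the model-based standardised risk differences. Define it as in Table 3, within 6 months before the health checkup, so that it is the variable already extracted. Justify it on prognostic grounds, without reference to the observed imbalance.
2. State that the odds ratio is then conditional on previous visiting as well as on the stratification factors.
3. Optionally, pre-specify participants with no previous visit as a subgroup. They are the people whom the Introduction describes as the gap to be closed.
4. Reconcile the 4.1–5.6% in Table 3 with the 7–8% in the Conclusions, stating the definition and population behind each figure.

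The cost is one binary term, one sentence on interpretation and, if wanted, one subgroup line. No new data and no change in sample size are needed.

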## Discussion

4

Large-scale CKD screening is criticized from the viewpoint of cost-effectiveness [20], but consensus has been obtained that the prevention of CKD progression is an important public health issue. Because Japan is a country where pre-diagnosis CKD data have been accumulated by nationwide health checkups, we could develop an efficient intervention after CKD screening and assess its effectiveness in the real world. Conventional CKD screening in Japan can detect potential CKD patients from the general population but lacks intervention to make them visit physicians after the screening. Consequently, we designed a pragmatic trial of nudging CKD patients to visit physicians after screening. The results from this trial will contribute to filling the gap between screening and subsequent medical interventions and will also be a model for a “learning health system” that utilize the routinely collected health data to improve the health care system.

Our pragmatic RCT is designed in the health care system. By taking advantage of having large-scale health checkup data in Japan, we are conducting this implementation research to improve patients' visiting behaviors to physicians after CKD screening. Since it is usually difficult to allocate intervention, i.e., whether to provide medical treatment, in a high-risk population, our intervention to encourage patients to visit physicians by just sending them a letter is a feasible and realistic approach for the prevention of CKD progression. Our intervention is inexpensive and can be implemented for other health issues in the future. We will only use routinely collected data from the health care system to identify eligible participants, follow them, and measure their outcomes. This makes it possible to perform a large-scale pragmatic RCT involving a wider population at a lower cost. Our pragmatic RCT can assess both short-term outcomes of patients’ visiting behavior and long-term outcome of renal function through analysis plans, in which we can manage statistical multiplicity.

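### The eGFR analysis is called a confirmatory closed test, but its entry condition does not control error jointly across the primary pairwise and eGFR claims

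*Protocol article*

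**What the plan says.** All of this is in the protocol article.

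- **Primary outcome (2.6.2 Data analysis).** A logistic model gives a Wald omnibus test of the three groups: "If the two-sided p-values by omnibus tests is <5%, we will conclude that there are statistically significant differences in outcome between the groups". After a significant result the investigators "will continue to perform pairwise comparisons in order to adjust for multiple comparisons". No numerical level is given for the pairwise tests.
- **eGFR (2.6.2).** "For the confirmatory analysis of the secondary outcome, we will apply the closed testing procedure". The rule is then spelled out: "only if the two-sided p-values by the omnibus test of the primary outcome are <5%, we will conduct the following analysis". The eGFR omnibus test has its own 5% threshold, "If the two-sided p-values by omnibus tests are <5%, we will conclude that there are statistically significant differences in outcome between the groups", and pairwise comparisons follow. The rule sets no condition on the primary pairwise results and does not split alpha.
- **Discussion (section 4).** The short-term visiting outcome and the long-term renal outcome are both said to be assessed "through analysis plans, in which we can manage statistical multiplicity".
- **Sample size (2.6.1).** The planning rates are 0.15, 0.20 and 0.25 for control, usual letter and nudge-based letter, with 850, 1700 and 1700 patients. Power is to be at least 80% overall and for every pairwise comparison.

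**The concern.** With three arms and one outcome, an omnibus test followed by unadjusted pairwise tests is a valid closed test. If all three rates are equal, the omnibus test protects. If exactly two are equal, only one true pairwise null is left.

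That argument does not carry over to two outcomes. Suppose the letters beat control but do not differ from each other. The primary omnibus null is then false, so the omnibus test is usually significant and the eGFR analysis goes ahead. Two true nulls remain: usual equals nudge on visiting, and no eGFR difference. Each can be rejected at 5%. A closed procedure would also need a 5% test of their intersection, and the plan has none.

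A report that follows the plan literally could present a nudge-versus-usual result and an eGFR result as parts of one multiplicity-controlled set of confirmatory claims, and that description would be wrong.

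**Working it through.** **Inputs.** Group sizes 850/1700/1700, rates 0.15/0.20/0.25, eGFR difference −3 and SD 10 (section 2.6.1). Two-sided 5% for each omnibus test, with the primary omnibus test as the only entry condition for eGFR (section 2.6.2). The pairwise level is not stated and has to be inferred.

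**Step 1: reproduce the stated power and infer the pairwise level.** Pooled chi-square, two-sided:

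| Comparison | Power at 0.05 | Power at 0.05/3 = 0.0167 |
|---|---|---|
| Control vs usual | 87.7% | 76.1% |
| Control vs nudge | >99.9% | >99.9% |
| Usual vs nudge | 93.7% | 86.4% |

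By simulation at 5%, all three pairs are significant together in 81.6% of trials and the omnibus test in more than 99.9%. Power for eGFR is also above 99.9%. The stated figures (at least 80% and at least 99%) are therefore reproduced at 5% per pair. At 0.0167, control versus usual would miss 80%. The sample size thus points to 5% per pair.

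**Step 2: formula.** Let a be the chance of a false primary pairwise claim, g the chance that the primary omnibus test is significant, and 0.05 the eGFR error once tested. With independent outcomes, and since a false pairwise claim can occur only after a significant omnibus test:

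joint error = a + 0.05g − 0.05a

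- g = 1, a = 0.05: 0.05 + 0.05 − 0.0025 = 9.75%, which equals 1 − 0.95².
- 0.15/0.20/0.20, with simulated g = 0.870 and a = 0.0497: 0.0497 + 0.0435 − 0.0025 = 9.07%.

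**Step 3: simulation of the written sequence.** 400,000 trials per scenario, unadjusted chi-square tests for visits, normal eGFR group means with SD 10, independent outcomes. Each range covers two eGFR truths: no effect in any arm, and both letters shifted equally by 3 from control.

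| Visiting rates (control/usual/nudge) | Primary omnibus significant | Error, primary claims only | Joint error, primary + eGFR |
|---|---|---|---|
| 0.15/0.15/0.15 | 5% | 4.9–5.0% | 4.9–5.0% |
| 0.15/0.20/0.20 | 87% | 4.9–5.0% | 9.0–9.1% |
| 0.15/0.25/0.25 | about 100% | 5.0% | 9.7–9.8% |
| 0.15/0.15/0.25 | about 100% | 5.0% | 9.7–9.8% |
| 0.15/0.20/0.25 (planning rates) | >99.9% | 0 (no true null) | 5.0% |

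**Step 4: sensitivity.**

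- Outcome correlation of 0.1, 0.3, 0.5 and 0.8 at 0.15/0.25/0.25 with no eGFR effect gives 9.7, 9.7, 9.3 and 8.5%.
- If the primary pairs were tested at 0.0167 after all, 1 − (1 − 0.0167)(0.95) = 6.6%, still above 5%.

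**Step 5: a stricter entry condition.** If eGFR is tested only after all three primary pairs are significant, joint error is about 5% or less in every scenario in the Step 3 table. The eGFR test is then reached in about 82% of trials at the planning rates, but in only about 3% at 0.15/0.20/0.20 and about 5% at 0.15/0.25/0.25.

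**The case against.** The strongest defence is that the plan is a fixed sequence (primary omnibus, then eGFR omnibus) with protected pairwise tests inside each outcome, and that this sequence does what it needs to do. Much of that stands. Primary claims alone keep 5%, the eGFR error alone stays at or below about 5%, and no estimate, sample size or primary result changes. What does not stand is the label. The article names closed testing, calls eGFR confirmatory, includes pairwise tests in the multiplicity adjustment, and speaks in the Discussion of managing multiplicity over both outcomes. Since the article itself fixes the rule and names it, this is not a detail left to an analysis plan.

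A reader might infer more than the documents support:

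- **That the error is double a promised 5%.** No familywise figure is given for the pooled set of primary pairwise and eGFR claims, so there is no promised number to double.
- **That equal letters is the expected result.** The only planning assumption is three different rates, and there the joint error is 5.0%. Equal letters is a possible truth that strong control has to cover. Nothing ranks it as more probable than others.
- **That continuous visiting in Table 1 is an unprotected confirmatory test.** It is listed as a secondary outcome but never called confirmatory. The confirmatory sequence names eGFR only.
- **That the pairwise level is stated as 5%.** It is an inference from the reproduced power.

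**Conclusion.** The point holds as a mislabelled scope of error control. The written sequence controls error at 5% for the two omnibus hypotheses in order and for the pairwise tests within each outcome. It is not a closed test across primary pairwise and eGFR claims. There the joint error is about 9.0–9.8% with independent outcomes, and about 8.5% at a correlation of 0.8, when two arms have equal visiting rates, the third differs and eGFR is unaffected. It is about 5% when all visiting rates are equal or all differ.

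This rests on 5% pairwise tests and on unadjusted chi-square tests standing in for the planned adjusted Wald tests. The structural argument, that no test of the intersection exists, depends on neither.

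**What to change.** In section 2.6.2, state that 5% familywise control covers the two omnibus tests in sequence and the pairwise comparisons within each outcome, and nothing wider. Remove the closed-testing label as a description of the procedure across outcomes. Give the pairwise level explicitly. In the Discussion, qualify "in which we can manage statistical multiplicity" in the same way. Report the eGFR results as not jointly controlled with the primary pairwise claims. This costs no power or patients; the price is a slightly weaker claim for eGFR.

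If joint control is wanted, specify a true closed or graphical procedure over both sets of hypotheses. Requiring all three primary pairs to be significant before eGFR is tested would also hold 5%, but it is a real trade-off. eGFR would be reached in about 82% of trials at the planning rates and in only about 3–5% if the two letters work equally well, so a true letter-versus-control difference in eGFR would then almost never be tested.
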